### Quality control

To ensure the control group’s compliance, participants will receive the estazolam tablets of 1 week dose at the face-to-face interview every week, and sign on the medicine record of the CRF. In addition, our researcher will communicate with them every day to visit their medication via call, short message, or Internet connect tools.

All of the acupuncturists who take part in this trial have gained medical licenses in China and have been well trained according to the trial’s procedure under the guidance of senior acupuncturists. All of the investigators were qualified to perform this study after they participated in special training classes about this trial and were tested to well understand the research. For instance, they were trained to use the randomization number table, to fill in the case report form, to identify the correct acupoints, to manipulate the needles, and so on. Additionally, to ensure the quality of the study, the clinical monitors will check the process of the trial and document the details of the processes once a week. Moreover, monitors nominated by the principal investigator will check the accuracy and validity of the original data from the clinical center. Regular meetings will be held to consider the recruitment rate, adverse events, protocol violation, difficulties and problems emerging during the study, and so forth (Fig. 2).

**Fig. 2 Fig2:**
[figure not shown]
Trial processes chart. *PSQI* Pittsburgh Sleep Quality Index, *fMRI* functional magnetic resonance imaging, *MSMSMS* micro-movement sensitive mattress-type sleep monitoring system, *HAMD* Hamilton Depression Scale, *HAMA* Hamilton Anxiety Scale

## Discussion

This proposed study is a randomized, assessor–statistician-blinded, controlled clinical trial which is sponsored and financially supported by the National Nature Science Foundation of China. The purposes of this program are to evaluate the efficacy and safety of acupuncture for treating perimenopausal insomnia by assessing the sleep architecture, hormone level, and emotional-circuit neurological function, and to identify the effective mechanism of acupuncture regulating emotional center integration.

In the view that poor sleep quality during menopausal transition is closely related with mood disorder, the formula of acupuncture adopted in this trial will be based on syndrome differentiation from the liver. In recent years, there have been some published reports suggesting that treating insomnia according to syndrome differentiation from the liver is significantly effective [23, 24]. Some researchers investigated 3380 patients with insomnia in Shanghai and demonstrated that there are six basic types of insomnia: with hyperactivity of liver yang, stagnation of liver qi and blood, stagnation of liver qi invading the stomach, stagnation of liver qi invading the heart, fire derived from stagnation of liver qi, and wind derived from stagnation of liver qi [25]. On the basis of the syndrome differentiation from the liver, the previous study treated 2262 patients with sleep disturbance according to the therapeutic principle of soothing the liver, relieving depression, activating blood, and calming the mind; consequently it achieved a good curative effect [26]. Our pilot study also demonstrated that using acupuncture to treat perimenopausal insomnia from the liver is reliable and effective [14]. We therefore determined to design this study with the acupuncture intervention formula based on liver differentiation to provide evidence for the effects from clinical curative effect outcomes and the potential central mechanism.

Besides using the PSQI, MSMSMS, HAMD, and HAMA to assess the clinical curative effect, we choose fMRI technology to reveal the brain effective mechanism of acupuncture treatment for perimenopausal insomnia, as well as to provide clear, valid, and visual evidence.

There are several available evidence sources about acupuncture treating insomnia, perimenopausal syndrome, and emotional disorders [27–38]. Previous studies revealed the hippocampus volume of insomniac decreased notably [39–43] and acupuncture can improve insomnia significantly and change the brain region activity. Consequently, we hypothesize that acupuncture can improve perimenopausal insomniac with emotional problems via change in the correlated brain region’s activity, and we designed this study to assess the effects and research the influence of acupuncture for perimenopausal insomniacs.

There are also some accessed findings about several brain regions which are concerned with emotional problems. Previous studies suggested that the cerebral limbic system and the surrounding structure are the brain regions which are strongly linked with the affective state, as well as adjusted by frontal lobe, temporal cortex, and subcortex. Recent neuroimaging studies have implicated that several brain regions, including the orbitofrontal cortex (OFC), ventral medial prefrontal cortex (vmPFG), amygdale, hypothalamus, brainstem, cingulated cortex, thalamus, hippocampus, sensory cortex, and so on, play a key role in emotional regulation [44–46]. Meanwhile, other studies investigating the plasticity of emotional neurocircuitry and mood disorders also provide substantial support for the viewpoint that some brain regions, such as the prefrontal cortex, amygdale, hippocampus, and thalamus, are the critical sections of emotional neurocircuitry and exert an important effect on emotional regulation [47, 48]. Sleep disturbances may contribute to the weakened emotional regulation of the prefrontal cortex. Long-term insomniacs tend to build an inner emotion mechanism to relieve the stress of insomnia [49]. Moreover, findings of a cerebral functional imaging study declared that when the subcortex and autonomic nerve system are inhibited by the prefrontal cortex, a bad affective state including anxiety and depression will be generated [50, 51]. Some research considered that the amygdale may impact the plasticity of the hippocampus and thalamus [52, 53], whereas its plasticity is also influenced by regulation of the prefrontal cortex, which will inhibit negative emotion by connecting with the amygdale [54]. Given that the amygdale may be closely related with sleep disorder, previous studies revealed that when a primary insomnia patient turns to a sleep state from waking status there are abnormal activity brain regions including the amygdale, hippocampus, thalamus, and prefrontal cortex [55, 56]. Based on the possibility that the acupuncture signal may stimulate the central integration neural signal and improve emotional disorder, and the findings that there may be abnormal nerve function in the emotional neurocircuitry of insomniacs, it is hypothesized that the emotional neurocircuitry and emotional center cortex may integrate and respond to the acupuncture signal; during this procedure, central regulation of the prefrontal cortex and functional connection of the amygdale may play an important role. Thus, after the sleep-related center responded/answered acupuncture signal, positive regulation of the sleep architecture and mood disorder is able to improve sleep difficulties.

Nevertheless, there are also limitations in this study. Concerning the unfeasible blinding to participants, one limitation is the possibility of a high risk of bias regarding blinding by unconcealed allocation. We therefore strictly conduct randomization and separate the acupuncturist, assessor, and statistician. Meanwhile, patients divided into the acupuncture intervention group may have more opportunities to make contact with their acupuncturists and establish a good doctor–patient relationship rather than those of the western medicine control group, which is likely to improve the therapeutic effect [57]. Hence, we will maintain close contact with patients in the control group by telephone, Internet, and so on, to minimize this potential bias.

In conclusion, the results of this trial are expected to confirm whether an acupuncture formula based on liver differentiation is effective in relieving perimenopausal insomnia. Combining neuroimaging with a neurophysiology method, the relevant outcomes are predicted to verify the central mechanism of acupuncture treatment. We believe that the results will exert a positive effect on acupuncture treatment for perimenopausal insomnia (Additional files 1 and 2).

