**Methods/Design:**

This study is a randomized, assessor–statistician-blinded, positive medicine controlled trial involving 40 participants. A total of 40 eligible patients with perimenopausal insomnia will be randomly assigned to two groups in a 1:1 ratio as an intervention group using acupuncture and a control group taking estazolam. Participants in the intervention group will receive six acupuncture treatment sessions per week for 4 consecutive weeks, for a total of 24 sessions during the study. Meanwhile, the medicine control group will be prescribed estazolam 1–2 mg/day to be taken 30 minutes before sleep for 4 weeks. The primary outcome is the Pittsburgh Sleep Quality Index. Secondary outcomes are the micro-movement sensitive mattress-type sleep monitoring system, the Hamilton Depression Scale, and the Hamilton Anxiety Scale. All outcomes will be evaluated before and after treatment. The safety of interventions will be assessed at every visit.

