## Background

Every woman has to undergo the menopausal transition as an inevitable stage of life. During this period, perimenopausal females usually complain of difficulties initiating and/or maintaining sleep with frequent nocturnal and early morning awakenings. Sleep disturbances are often multifactorial in origin and have a significant impact on the health-related life quality. The Study of Women’s Health across the Nation (SWAN) presents that the prevalence of sleep disturbance ascends with increasing age. Recent reviews revealed that the prevalence of insomnia in the perimenopausal women ranges from 39 to 47% [1], while it is approximately 35% in the general population [2].

In addition, with the increasing socioeconomic stress, there are more and more middle-aged women suffering from mood disorders, such as anxiety and depression, which have been noted to be closely related to sleep problems in postmenopausal women [3]. Difficulty in falling sleep has been shown to associate strongly with anxiety, with nonrestorative sleep also correlating strongly with depression, as well as results in anxiety, irritability, and nonrefresh sleep problems which in turn may manifest as depression [4]. Studies by Guidozzi et al. [5] also showed a significant correlation between depression and sleep-related disorders. According to these findings, sleep difficulties and emotional problems interact with and aggravate each other.

Currently, hypnotic medication such as benzodiazepine receptor agonists (estazolam in particular) has been recommended to be the first-choice medicine used routinely for chronic insomnia. Although estazolam is efficacious in the short-term management of insomnia, there is very limited evidence for long-term treatment efficacy [6]. Additionally, various adverse effects related to their use have been reported, including residual daytime sedation, cognitive impairment, and medication dependence [7–10]. Therefore, a large number of patients with insomnia are turning to complementary and alternative medicine such as acupuncture rather than hypnotic medication.

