### Hypothesis

According to the validity of acupuncture on perimenopausal syndrome, insomnia, and emotional disorder, as well as the influence of acupuncture on brain function, we hypothesize that acupuncture will improve the symptoms of perimenopausal insomniacs, and there will be a difference between acupuncture and medicine control based on the fMRI examination.

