### Primary outcome

#### Pittsburgh Sleep Quality Index

The Pittsburgh Sleep Quality Index (PSQI), a self-rated questionnaire that evaluates sleep quality and disturbance over 1 month [20], is applied as the primary outcome measurement for clinical effectiveness assessment. The constructive validity and reliability of the PSQI to measure changes of sleep quality have been confirmed in previous studies all over the world. It is widely used to measure response to treatment in research studies and clinical trials. The PSQI is comprised of 19 items which consist of the following seven component scores: subjective sleep quality, sleep latency, sleep duration, sleep efficiency, sleep disturbance, use of hypnotic medication, and daytime dysfunction. Each item is weighted equally on a 4-point scale, from 0 to 3, with 0 indicating no dysfunction and 3 indicating the worst dysfunction. The seven component scores are then added to provide a global PSQI score. In general, a lower global score reflects a better sleep quality [21].

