### Statistical analysis

In this study, statistical analysis will be performed by a professional statistician blinded to the whole trial process using SPSS19.0 statistical software, and based on the intention-to-treat principal and preprotocol population. All demographic, baseline characteristics, curative effects, and fMRI images of the subjects will be analyzed with different approaches.

In terms of the data description, the enumeration data/quantitative data will be expressed with/as a percentage or proportion, while the measurement data/qualitative data will be represented as average and standard deviation. On this occasion of normal distribution and homoscedasticity, one-way analysis of variance (ANOVA) will be applied to identify differences in measurement data/qualitative data of comparison. Other covariates will be considered for further revision and if necessary stated in the statistical analysis project prior to data lock. Similar analysis of covariance (ANCOVA) models will used for secondary analysis to adjust baseline characteristics. A *q* test (Newman–Keuls) will be used for pairwise comparison. In case of nonnormally distributed data and heteroscedasticity data, a nonparametric test (Kruskal–Wallis *H* test) will be performed, and a rank sum test (Nemenyi) will be conducted to identify difference between groups. The enumeration data/quantitative data will be compared by chi-square test, while classification data will be evaluated with a rank sum test. In addition, the exploratory analysis will be implemented to describe group means over time. A two-sided test will be applied for available data and *p* < 0.05 will be taken as significant for each outcome. Missing data will be explored and if necessary multiple imputations will be utilized.

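### The protocol aims to show that acupuncture is effective, but its only randomised comparison is a difference test against active estazolam, which cannot by itself establish that unless acupuncture proves superior

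*Protocol article*

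**What the plan says.** **Aim and conclusion.** The Hypothesis section reads: "we hypothesize that acupuncture will improve the symptoms of perimenopausal insomniacs, and there will be a difference between acupuncture and medicine control". The sentence ties that difference to the fMRI examination, so its clinical half has no comparator. The last paragraph of the Discussion says that "the results of this trial are expected to confirm whether an acupuncture formula based on liver differentiation is effective in relieving perimenopausal insomnia". Both statements are absolute: they concern whether acupuncture works, not how it compares with something else.

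**A comparative statement elsewhere.** The Background section says that effectiveness and central mechanism will be investigated with fMRI through a comparison with western medicine. It gives no direction for that comparison and no criterion of success.

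**Design.** The Abstract calls the study a "positive medicine controlled trial involving 40 participants", with patients "randomly assigned to two groups in a 1:1 ratio as an intervention group using acupuncture and a control group taking estazolam". There is no sham, placebo, waiting-list or untreated arm. The Background says of the comparator: "Although estazolam is efficacious in the short-term management of insomnia".

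**Endpoint and analysis.** PSQI "is applied as the primary outcome measurement for clinical effectiveness assessment". It is self-rated, and one of its seven components is use of hypnotic medication. The Statistical analysis section compares groups by ANOVA, or by Kruskal–Wallis where assumptions fail, with ANCOVA as secondary. It adds: "A two-sided test will be applied for available data", with significance at 0.05 for each outcome. The article states no superiority, non-inferiority or equivalence objective for PSQI, and no margin.

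**The concern.** The question that the protocol poses and the question that its randomised comparison answers are different. The test asks whether PSQI differs between acupuncture and estazolam. The Hypothesis and the concluding paragraph ask whether acupuncture relieves perimenopausal insomnia.

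Two results are easy to imagine, and neither would settle the stated aim. In the first, both arms improve and the difference is not significant. In the second, the acupuncture arm improves from baseline. The first shows neither effectiveness nor equality with estazolam, because no margin was set and the estimate will be imprecise. The second is not a randomised comparison and cannot separate a treatment effect from natural course or expectation. With the aim worded as it is, either result could be offered as confirmation. The choice of framework belongs in the protocol, and an analysis plan cannot make a two-arm active-control difference test answer an absolute question.

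**Working it through.** **1. What each PSQI result would say about the stated aim**

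| Result | What it supports | Does it show that acupuncture is effective? |
|---|---|---|
| Acupuncture significantly better than estazolam | Superiority over a drug taken to be efficacious | Indirectly, and weakly: patients are unblinded, the outcome is self-rated, and its hypnotic-use component counts against the estazolam arm |
| No significant difference | The range of differences inside the confidence interval | No; nor does it show equality without a margin |
| Estazolam significantly better | Acupuncture is inferior to estazolam | No; it could still be better than nothing, but there is no arm to show it |
| Improvement within the acupuncture arm | A before–after change | No; there is no concurrent untreated comparison |

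**2. Inputs**

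- n = 20 per arm (Sample size section); two-sided α = 0.05 (Statistical analysis section).
- PSQI SD: not in the protocol. Assumed 3 to 4 points.
- True disadvantage of acupuncture: not in the protocol. 0.5 SD is used as an illustration.

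The article's own figure of 40 cannot be re-derived for PSQI. It rests on a minimum of 10 per group for fMRI, on earlier trial experience and on a withdrawal rate that is not given as a number. No PSQI effect size, SD, power or margin is stated.

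**3. Precision of the between-arm difference**

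Half-width of the 95% interval = t(0.975, 38) × SD × √(2/20) = 2.024 × 0.316 × SD = 0.64 SD.

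| Assumed SD | Half-width (PSQI points) |
|---|---|
| 3 | 1.92 |
| 3.5 | 2.24 |
| 4 | 2.56 |

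An observed difference of exactly zero would thus be compatible with estazolam being better by about 1.9 to 2.6 points.

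**4. Chance of a non-significant result when acupuncture is worse**

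For a true difference of 0.5 SD the non-centrality parameter is 0.5 × √(20/2) = 1.58 on 38 degrees of freedom. Power of the two-sided t test is 33.8%, so the chance of p ≥ 0.05 is 1 − 0.338 = 66%. Power is about 10% for a true difference of 0.2 SD and 69% for 0.8 SD.

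**5. Would adding a non-inferiority objective rescue the present size?**

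The smallest margin that 20 per arm supports with 80% power (one-sided 0.025, true difference zero) is (1.960 + 0.842) × √(2/20) = 0.886 SD. That is 0.886 × 3 = 2.7 to 0.886 × 4 = 3.5 points. A margin of 2 points would need 36 per arm at SD 3 and 63 per arm at SD 4. Non-inferiority is therefore not simply available by changing the wording.

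**The case against.** **The protocol does frame effectiveness comparatively.** The Background section speaks of a comparison with western medicine, and the Abstract identifies an active control. This stands, so it would be wrong to say that only the imaging question is comparative. It makes the framing inconsistent rather than uniformly absolute. It does not say which way PSQI should differ or how a difference test would become a finding of effectiveness.

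**Superiority over estazolam would support effectiveness.** This also stands, on the protocol's own premise that estazolam works in the short term. A reader might infer that the design can say nothing at all about effectiveness; that goes too far. The route is nevertheless not hypothesised, and it is weak for the reasons in the first row of the table.

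**No rule in the protocol misreads anything.** A reader might infer that the trial will report p > 0.05 as equality, or that it plans a within-arm PSQI test. The documents support neither. The Statistical analysis section describes group comparisons and only descriptive group means over time; the paired test in the fMRI data processing section concerns cortical measures. The risk comes from how the hypothesis and conclusion are worded. The quoted conclusion is also a closing remark, phrased as an open question.

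**Two tempting supporting arguments should not be leaned on.** The entry floors on the Hamilton depression and anxiety scales could produce regression to the mean in those secondary outcomes. PSQI has no entry floor, so any effect on it is indirect. The Discussion's concession about greater contact concerns bias between the arms, for which close contact with controls is planned; it does not explain within-arm change.

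**The figures are illustrative.** The SD and the 0.5 SD difference are assumptions, and the secondary ANCOVA could narrow the interval. That is fair, but narrowing the interval does not alter the mismatch of question and comparison.

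**Conclusion.** The point holds, as a mismatch between the stated aim and the randomised comparison. The design cannot by itself establish that acupuncture is effective unless acupuncture is shown superior to estazolam, which the protocol does not hypothesise. A non-significant PSQI difference would be open to misreading, and it is a likely result if acupuncture is similar to estazolam or moderately worse.

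The 0.64 SD half-width follows from 20 per arm alone, with every patient analysed and no covariate adjustment. The conversion to points depends on the assumed SD, and the 66% on the illustrative difference of 0.5 SD. The qualitative conclusion needs none of these assumptions. This should be corrected, but it is a fault in what the trial says it will conclude, not in the planned test of difference.

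**What to change.** 1. **Hypothesis:** state the primary clinical hypothesis as a two-sided between-arm difference, acupuncture versus estazolam, in PSQI at end of treatment.
2. **Statistical analysis:** report that difference with its 95% confidence interval. State that neither p ≥ 0.05 nor change within an arm will be taken as evidence of effectiveness or of equal efficacy.
3. **Discussion:** limit the expected conclusion to the effect relative to estazolam, and bring the Background's comparative statement and the Hypothesis into line with it. Add the lack of an inactive control to the limitations, which now cover only blinding and contact.

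The cost is a less favourable claim. No new patients or data are needed, the between-group test is already planned, and the article describes the trial as still recruiting, so the wording can be settled before results are known.
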